# Enhancing Executive Functions Among Dutch Elementary School Children Using the Train Your Mind Program: Protocol for a Cluster Randomized Trial

**DOI:** 10.2196/resprot.7908

**Published:** 2018-06-07

**Keywords:** executive function, children, socioemotional development, cognitive development, academic performance, physical activity, healthy eating, eHealth

## Abstract

**Background:**

Executive functions are higher cognitive control functions, which are essential to physical and psychological well-being, academic performance, and healthy social relationships. Executive functions can be trained, albeit without broad transfer, to this date. Broad transfer entails the translation of improved cognitive functions to daily life (behaviors). The intervention Train your Mind was designed to train executive functions among elementary school children aged 9 to 11 years, and obtain broad transfer in terms of enhanced physical activity, healthy eating, and socioemotional regulation.

**Objective:**

This paper aims to describe the cluster randomized trial to test the effectiveness of the Train your Mind intervention.

**Methods:**

Train your Mind was integrated into the existing school curriculum for 8 months (25 weeks excluding holidays). The effectiveness of the intervention was tested in a cluster randomized trial comprising 13 schools, 34 groups (school classes), and 800 children, using a battery of 6 computer tasks at pre- and postmeasurement. Each of the 3 core executive functions was measured by 2 tasks (Flanker and Go/No-Go; N-Back and Running Span; Attention Switching Task and Dots/Triangles). Moreover, we administered questionnaires that measure emotion-regulation, cognitive errors, physical activity, dietary habits, and the psycho-social determinants of diet and physical activity. Body mass index was also measured. Multilevel analyses will account for clustering at the school and group levels, and randomization took place at the school level.

**Results:**

Results are currently being analyzed.

**Conclusions:**

The main purpose of this study is to test Train your Mind’s effectiveness in enhancing executive functions. Second, we investigate whether increased executive functions lead to improved physical activity and healthy eating. If found effective, executive function training could easily be integrated into school curricula everywhere, and as such, boost health, academic performance, and emotion-regulation of elementary school children, in a cost-effective manner.

**Trial Registration:**

Netherlands Trial Register NTR5804; http://www.trialregister.nl/trialreg/admin/rctview.asp?TC=5804 (Archived by WebCite at http://www.webcitation.org/6z9twosJ8)

**Registered Report Identifier:**

RR1-10.2196/7908

## Introduction

### Background

Executive functions (EFs) are higher mental control functions, consisting of impulse control, working memory and cognitive flexibility [1,2]. EFs are vital to a myriad of areas in life, including physical [3,4] and psychological well-being [5], academic performance [6], and healthy social relationships [7]. EFs can be trained [8,9]. However, such strengthened cognitive functions have, as of yet, not been accompanied by meaningful, behavioral improvements in daily life—otherwise known as broad transfer [10,11]. Recent literature suggests (combining) multiple approaches to train EFs and subsequently attain broad transfer [2,10]. Train your Mind (TyM) follows these recommendations, and as such, applies 3 main modules to train EFs: (1) focused physical activity, (2) cognitive games, and (3) socioemotional development. A fourth module, (4) tailored feedback (eHealth), aims to directly change the behaviors physical activity and healthy eating. These modules are presented in great depth in a separate paper, including the development and implementation ([name] et al, unpublished data, 2018). An extensive background on what EFs are, how they can be trained, and why they are so pivotal to a healthy and successful life is described in the same separate paper ([name] et al, unpublished data, 2018). This paper focuses on the study design and outcome measures.

### Aims and Hypotheses

This study’s main objective is to enhance EFs, among 9- to 11-year-old elementary school children, through a multimodule intervention combining physical, cognitive, and socioemotional approaches. Longitudinal EF studies have revealed a substantial amount of positive correlates, including physical and mental well-being, level of education, job income, marital harmony, substance use, unsafe sex, risky driving, eating, and social relations [2,4,5]. This lead us to expect improved EFs to translate into healthier behavior in daily life (especially considering our multidimensional, integrated intervention), more specifically, in our target population. As a result of stronger EFs, we expected the children to be physically more active and eat more healthily. Such daily life improvements as a result of strengthened EFs would constitute the much-desired broad transfer. This broad transfer is hypothesized to be mediated by EFs. To bridge the seemingly distant cognitive control functions with physical activity and eating, it may help to consider self-regulation, concentration, and attention. It is easier to envision how the latter are improved as a result of stronger EFs (eg, inhibitory control can shut out distracting stimuli, keeping the mental working space clear, but also maintaining optimal levels or emotional and cognitive arousal, by self-regulation). In sum, the model we are working with assumes a 3-level cascade effect: (1) increased EFs will lead to (2) improved self-control, emotion-regulation, and attention, which in turn will facilitate (3) healthy eating and physical activity.

#### Main Hypothesis

The main hypothesis is as follows:

EFs are enhanced through a multi-dimensional intervention (TyM).

#### Secondary Hypotheses

The secondary hypotheses are as follows:

TyM effects transfer to improved:

Emotional-regulationConcentration/attention

TyM effects translate to other aspects of daily life, specifically:

More physical activityHealthier dietary habitsReduced social/emotional/behavioral problemsBetter school performanceThese broad transfer effects are mediated by stronger EFs

## Methods

### Trial Design

The effectiveness of TyM was investigated in a cluster randomized trial comprising 13 elementary schools, with a total of 34 groups and 800 children. Schools in the control condition continued their regular school curriculum, and would receive the program, or any components thereof, after the third and final measurement (follow-up) had been completed. In this sense, it was a passive control group (though the same amount of time will be spent on similar activities, gym sessions, etc, minus the explicit EF training). All groups of the Dutch sixth and seventh grade of schools in the experimental condition followed the entire TyM intervention for 8 months (25 weeks excluding holidays). This means it is nearly impossible to determine effectiveness per component—our study was set up primarily to answer the question: Can EFs be enhanced through a multi-dimensional training program? If satisfactory results are obtained, TyM can be disentangled in the future to further scrutinize each component separately. Children were to be measured at 3 different time points: preintervention, postintervention, and at follow-up 6 months later. However, the follow-up could not be organized due to financial constraints.

### Participants and Procedure

The promising potential that lies in training EFs (academic performance, healthy behaviors, better social relations) was presented to education foundations (Movare and Innovo) in South-Limburg, The Netherlands. Interested school directors and teachers further inquired about the willingness of other teachers to participate. A total of 13 schools, 34 groups, representing 800 pupils, decided to participate in TyM. Every sixth or seventh grade pupil (aged 9-11 years) of a participating school automatically took part in the intervention activities, as they were integrated in the existing school curriculum. Participation in measurements, on the other hand, could be refused by parents. Every child of the relevant school classes was welcome to join; we assumed normally distributed groups in terms of attention problems and fluid intelligence.

### Ethics and Consent to Participate

Consent was obtained from the schools. Both parents and children were informed about the intervention and measurements, and both parents (written) and children (verbal) were asked to provide consent. Parents and students can withdraw from participation at any time. This intervention, along with the study methods and consent procedure, were approved by the Ethical Review Committee of the Faculty of Psychology and Neuroscience, Maastricht University, the Netherlands (dd. 13-08-2015, ERCPN-06-06-2015).

### Availability of Data and Materials

Data are not yet available. Materials can freely be requested from [contact].

### Randomization

Schools, matched by number of pupils in the participating grades, and from similar areas, were randomly assigned to either an experimental or a control condition, by means of a coin toss (simple randomization) performed by the first author of this paper. Before this process, however, 3 schools had to be assigned a condition because they would not participate otherwise. One school could only participate as a control school because they had large infrastructure works scheduled for the school year and did not want to overly burden the teachers in that hectic period. Two schools were so interested in training EFs they would only agree to participate as experimental schools, as they wanted to train EFs regardless (they could not guarantee respecting the terms of being a control school). We decided to include all the 3 schools anyway, because in any case, it would offer us valuable insights in how our novel and ambitious intervention would work in the field, especially at highly motivated schools. Because it had not yet been (sufficiently) proven in previous studies that EFs can be trained, we decided to maximize our chances of finding an answer to the most fundamental research question of our project: can EFs be trained? (by TyM). Furthermore, all schools were highly motivated to participate. This flaw in the randomization process will be taken into account during analysis.

### Intervention

TyM combines (1) focused physical activity, (2) cognitive games, and (3) socioemotional development in an attempt to enhance EFs. Physical activity and healthy eating are directly targeted in a fourth module (4) tailored feedback (eHealth). To this date, it has proven challenging to sustainably train EFs, and even more so to achieve broad transfer [10]. Leading experts in the field suggest considering novel angles such as the mind-body connection and socioemotional balance [2,10,12-15]. The development, implementation, and content of these modules are described in great detail in a separate paper ([name] et al, unpublished data, 2018). A brief description of the intervention is presented in the following paragraphs.

Promising results with regard to training EFs were found by a yoga [15] and a taekwondo intervention [13,14]. For TyM, core elements of kung fu were comprised into the focused physical activity component, as the fundamental idea of kung fu is self-control (achieved through rigorous training aimed at intrapersonal progress—it is by nature not competitive). After initial workshops (for teachers) and introductory lessons (from our kung fu expert to the participating class groups), teachers lead the kung fu sessions themselves, during physical education hours at school (1 hour/week), supported by a teaching manual.

Despite an apparent lack of groundbreaking results for cognitive training within the field of EF training [2,10,16], we reasoned that this angle still merited a place in our multidimensional intervention. The idea was that effects of singular components could multiply synergistically in an integrated whole. Moreover, approaches could be combined in applications, such as cognitive and socioemotional training while playing board games (handle losing, cheating). The TyM collective cognitive games included (1 hour/week): SET, charades, taboo, and memory. Theoretically, the most appropriate games for EF training are challenging and engage multiple EF subcomponents simultaneously [2,8] (eg, SET).

Furthermore, to ensure an incremental challenge at the individual level, individual Web-based games were presented (Cambridge Brain Sciences), including adapted Raven’s progressive matrices, Stroop, paired-associate learning, Hampshire tree task, and spatial working memory/planning.

An effective guide to address socioemotional development while training EFs was found in MindUp [17], in which children learn to recognize and handle emotions in a more functional way [18,19]. The core technique of mindful breathing aids children in finding and maintaining their composure. Pupils learn more about the relationships between thoughts, emotions, and behavior. We adapted the existing MindUp program to our own Dutch target population. All schools already had some kind of socioemotional development program (and allotted weekly time slot), which was replaced by our unified version of MindUp (30 minutes/week for the duration of the trial (25 weeks, excluding holidays), including what we believed were essential components (such as mindful breathing). A teaching manual with additional background information, suggested lesson structures, and hints supported the teachers for these sessions.

The latter 3 modules target EF training, whereas our fourth TyM module aims to change behavior directly; personalized feedback/advice regarding physical activity and healthy eating is generated based on psycho-social determinants that are assessed in the Web-based eHealth module. The feedback is construed through behavior change models such as Reasoned Action Approach [20] and Theory of Planned Behavior [21].

Control groups continued their regular curricula.

### Primary Outcomes

At the core of our intervention and study lied EFs. These EFs were measured using a computerized task battery consisting of 6 tasks (2 per EF subcomponent), consistent with most recent suggestions from the field [2,22,23]. Careful attention was paid to the fact that testing and training tasks must be adequately different, so as to avoid practice effects (ie, merely measuring children’s improvement on 1 [near-] similar task that they have repeated/practiced over and over).

 In terms of the measurements themselves, we hoped that any practice effects would be minimized by the long periods of time in between pre, post, and follow-up measurements (7 and 6 months, respectively), by the fact that there was a control group and, most importantly, by the fact that the measurement tasks were sufficiently different from the (Web-based) cognitive training tasks. Both original tasks and adapted versions of existing tasks were included in this task battery. The entire battery was pilot-tested in a small study investigating the effectiveness of a 6-session kung fu intervention designed to enhance EFs. As a result, the task battery was fine-tuned and any final glitches were ironed out; it takes about 1 hour and 15 min to complete it the first time. In the section below, we provide an overview and descriptions of the tasks per EF subcomponent.

### Secondary Outcomes

As the development of EFs is boosted, we hypothesize various daily life behaviors to benefit from this as well (see secondary hypotheses for an overview of the aspects this study focused on). These outcomes constitute the aforementioned broad transfer and practical relevance of increased EFs; other than stronger EFs, what are the potential benefits for the individual? The case for physical activity and healthy eating is peculiar, as they can not only be affected by increased EFs but also by the tailored feedback eHealth module, which specifically targets these 2 behaviors. 

The eHealth module operates a behavior change model that is almost entirely driven by determinants (of the targeted behaviors), assisted by additional behavior change techniques such as coping plans. These determinants are measured by the program, during the intervention, as personalized feedback is offered to the individual, in response to these determinants and how they evolve over time. However, the very same determinants are also included in the large pre and post-intervention measurements, to allow for comparison with the control group. Measuring these determinants allows us to investigate what changes in determinants drove the change in behavior—useful knowledge in light of similar future behavior change interventions. An overview of the outcome measures is presented in Textbox 1.

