## Discussion

This study design protocol describes the cluster randomized trial to test the effectiveness of TyM, an intervention designed to enhance EFs among elementary school children aged between 9 and 11 years. Multiple modules (focused physical activity, cognitive games, and socioemotional development) are combined in TyM to increase the chances of EFs to improve and broad transfer to occur (translation of cognitive effects into daily life improvements, such as physical activity, adaptive emotion regulation, and healthy eating). Although broad transfer has not yet been demonstrated in the field, leading experts suspect combining approaches may yield promising results [2,10-12]. TyM is novel in the sense that it combines a physical-, cognitive-, and socioemotional approach in one integrated program. The development of the intervention and why EFs are of such cardinal importance to a healthy and happy life are described in a separate paper ([name] et al, unpublished data, 2018). EFs are the very core of the entire project, which is why careful attention was paid to the measurement of these. An extensive 1 hour computer task battery was designed, with 2 tasks per sub-EF; impulse control: Flanker and Go/No-Go; working memory: N-Back and Running Span; cognitive flexibility: Attention Switching Task and Dots/Triangles. Additionally, questionnaires measured attention, concentration, emotion-regulation, social/behavioral problems, physical activity, and healthy eating. BMI was also measured. The TyM data will be enriched with academic performance and socioeconomic status from a provincial database to investigate the relations between our variables of interest. We hope to shed more light on the intricate connections between EFs, healthy behaviors, academic performance, and emotion regulation. Considering the vast array of possible positive outcomes of training EFs, efforts in this direction are warranted and justified. Given the intense nature of optimal cognitive training, and significant personal differences, combining various approaches in a playful context seemed like something teachers and pupils could continue doing wholeheartedly for a longer period of time.

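### Emotion regulation is counted as transfer from stronger executive functions although the third module also teaches it, and neither the second-route caveat nor the mediation analysis covers it

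*Protocol article*

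**What the plan says.** The abstract states the aim of training EFs in order to "obtain broad transfer in terms of enhanced physical activity, healthy eating, and socioemotional regulation", having just defined broad transfer as better cognitive functions carrying over into daily behaviour. The Discussion repeats the idea as the "translation of cognitive effects into daily life improvements, such as physical activity, adaptive emotion regulation, and healthy eating". Aims and Hypotheses sets out a three-step cascade in which "increased EFs will lead to (2) improved self-control, emotion-regulation, and attention", and these in turn favour healthy eating and activity. Secondary Outcomes refers the reader to the whole list of secondary hypotheses and describes the outcomes there as what broad transfer consists of.

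The Intervention section describes the third module as an adaptation of MindUp "in which children learn to recognize and handle emotions in a more functional way", with mindful breathing and lessons on how thoughts, emotions and behaviour relate. The module is delivered as "our unified version of MindUp (30 minutes/week for the duration of the trial (25 weeks, excluding holidays"). The same section then classifies the modules: "The latter 3 modules target EF training, whereas our fourth TyM module aims to change behavior directly".

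Secondary Outcomes makes one exception to the EF route: "The case for physical activity and healthy eating is peculiar, as they can not only be affected by increased EFs" but also by the tailored-feedback module. Statistical Analyses names the mediation analysis (Baron and Kenny, with EFs as covariate) for physical activity and healthy eating only.

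**The concern.** An outcome can show transfer from EFs only if the programme reaches it through EFs, or if the part that goes through EFs can be told apart from the rest. The article applies this reasoning to physical activity and diet, where it points out that a module also aims at the outcome itself. It does not apply it to emotion regulation, although its own account of the third module has children being taught to deal with emotions. The FEEL-KJ asks how a child deals with anxiety, sadness and anger, which is the same territory.

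What is at stake is the permitted conclusion. The article presents broad transfer as the result that the field has not yet shown. A FEEL-KJ gain that reflects only what was taught in the socioemotional lessons could be offered as evidence for it, and nothing in the text as it stands would prevent that.

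**Working it through.** The plan gives no figure on this point, so the check sets the sections side by side.

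**1. Status of each outcome named as broad transfer in the abstract**

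| Outcome | Module that also addresses it (Intervention) | Second route acknowledged (Secondary Outcomes) | EF mediation analysis named (Statistical Analyses) |
|---|---|---|---|
| Physical activity | Module 4, eHealth | Yes | Yes |
| Healthy eating | Module 4, eHealth | Yes | Yes |
| Socioemotional or emotion regulation | Module 3, adapted MindUp | No | No |

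Emotion regulation has the same structure as the other two, but neither of the safeguards.

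**2. What an arm difference on the FEEL-KJ contains**

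Let *a* be the programme effect on EFs, *b* the effect of EFs on emotion regulation, and *d* the effect of the third module that does not pass through EFs. Then

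total difference = *a* × *b* + *d*.

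The cascade in Aims and Hypotheses contains only the first term. If *a* = 0, the total is *d*, which need not be zero. A comparison of arms estimates the sum. Separating the terms needs an analysis that includes EFs, and the one named in the article does not extend to this outcome. Trial Design concedes that the effects of single components can hardly be separated, so the design does not separate them either.

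**3. How large *d* might be**

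Scheduled time in the third module is 0.5 h per week × 25 weeks = 12.5 h per child in the experimental arm. This is not a difference between arms. According to the Intervention section, all schools already had a socioemotional programme with a weekly slot, and the adapted MindUp replaced it. Control schools kept their regular curricula, and Trial Design says similar activities would fill the same amount of time there. The contrast is therefore one kind of socioemotional lesson against another. The documents give no basis for a numerical value of *d*. They show only that the arms differ in how emotion handling is taught, so *d* = 0 cannot be assumed.

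**4. Separation of training from testing**

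Primary Outcomes requires test tasks and training tasks to be sufficiently different, so that a gain is not mere practice. That safeguard is stated for the EF tasks. No counterpart is stated for the questionnaires.

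**The case against.** The case on the other side has several sound parts.

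- **Wording of the hypothesis.** Secondary Hypotheses says "TyM effects transfer to improved" emotional regulation and attention, so the subject is the programme and not EFs, and the mediation sentence closes the other list. This is correct for that section. The abstract, Secondary Outcomes and the Discussion nevertheless attach the broad-transfer label to emotion regulation.
- **The authors' own model.** Aims and Hypotheses says that broad transfer is hypothesised to be mediated by EFs, so a gain without mediation would not satisfy it. This also stands. A reader might infer that the plan announces it will treat a FEEL-KJ difference alone as transfer, but no section says so. The point is that the text leaves that reading open and names no analysis that would test it.
- **Lesson time.** A reader might take the 12.5 hours as extra exposure in the experimental arm. The documents do not support that, because the lessons replaced an existing slot.
- **Overlap of content.** The FEEL-KJ covers 15 strategies, among them distraction, forgetting and social support. The third module is described only in general terms, with detail left to a separate paper. Overlap at the level of single strategies cannot be verified. Overlap at the level of handling emotions is plain from the text.
- **Purpose of the module.** The authors use MindUp as a vehicle for EF training. The Intervention section presents it as addressing socioemotional development at the same time, so it has both aims.

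A reader might also conclude that broad transfer should be reserved for school performance (CITO) and the SDQ conduct and peer scales, as the outcomes no module teaches. The documents do not support that list. The board games include practice in coping with losing and cheating, the third module covers behaviour as well as emotions, and the example item for the SDQ conduct scale concerns lying or cheating. The list also leaves out attention (ARCES), which stands beside emotion regulation in the secondary hypotheses.

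**Conclusion.** The point holds in limited form. The article labels emotion regulation as broad transfer from EFs, describes a module that also teaches it, and gives neither the caveat nor the mediation analysis that it gives to the two comparable outcomes. A FEEL-KJ difference could therefore be read as transfer from EFs without any change in EFs.

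The effect is on interpretation, for one family of secondary outcomes. The primary EF comparison, the data and the multilevel model are untouched. The size of the direct route is unknown and may be small, since control schools had socioemotional lessons of their own.

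The conclusion rests on two assumptions: that the adapted MindUp differs from the usual lessons in how it teaches children to handle emotions, and that the FEEL-KJ is sensitive to that teaching. Both are reasonable from the descriptions given, and neither is demonstrated. The SDQ emotional problems scale is a likely further case, but less certain than the FEEL-KJ.

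**What to change.** 1. In Secondary Outcomes, extend the second-route caveat to emotion regulation: the FEEL-KJ, and the SDQ emotional problems scale as a likely case. Adjust the sentence in Intervention that presents the fourth module as the only one acting directly.
2. State that an arm difference on the FEEL-KJ is reported as a total effect of the programme, compared with the schools' usual socioemotional lessons.
3. Extend the EF mediation analysis in Statistical Analyses to the FEEL-KJ, and call an effect transfer from EFs only if that analysis supports it.

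The cost is one more mediation analysis, some rewording and a narrower transfer claim. No new data are needed. The article says that the analysis was not yet complete, so the rule can be fixed before the results are interpreted.
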